^a^Exclusion criteria is valid for the primary data analysis only. Low values indicate less pain and improved function: 0 points = no pain and maximum physical functioning respectivelyThe exercise intervention is accessible at 55 locations (study sites) of the country, offering 85 exercise courses each half year. The number of participants per exercise course is restricted to twelve persons. The recruitment period covers two course terms. Assuming twelve participants in each course, the intervention can be provided to approximately 2000 insurants. Eligible patients can participate on condition that their physicians prescribe the health care offer. Interested patients register for the intervention program at the location nearby and will be informed about the accompanying scientific evaluation of the exercise program. In this context, exclusion criteria are requested and only eligible patients will finally be allowed for the exercise intervention. Further details including the study information sheet for potential study participants, the informed consent and a check-list for all inclusion and exclusion criteria will be delivered by mail. This mail will be sent to each participant prior to the first training session. The mail further includes the self-administered questionnaires. In the context of all aforementioned stages it will be pointed out that study participation is not a presupposition for exercise participation. Eligibility of the patients to enter the exercise program and to participate in the study will finally be determined by checking the inclusion- and exclusion criteria for the exercise intervention 1st in the context of the first visit and 2nd by information recorded via the self-administered questionnaire at t0 (Table 1). Patients refraining from the study still are eligible to receive the exercise program.Feasibility of recruitmentWe estimate that the offered exercise courses will be booked by 1500 patients (corresponding to 75 % occupancy rate). We further estimate a pre-study drop-out rate of 50–60 % due to lack of interest in study participation or exclusion according to study criteria. Thus approximately 700 patients will be allocated to the trial.Recruiting and selection of the control group (CO)(1) In a first step the insurance ID of study participants will be forwarded to a specific department of the health insurance company. This department is responsible for the extraction of ten statistical controls for each study participant of the intervention group according to the procedure described in the statistical part of this manuscript. This pool of controls shall ensure the proper selection of one matched statistical twin for each participant in the second matching step according to number (5). The factor ten has already been proven successful in a previous study of the insurance company and was therefore adopted for the present study [18].(2) The address and insurance number of the selected statistical controls according to (1) will be forwarded to another department of the company. This department will then forward study details (study information sheet for participants, informed consent form, questionnaires) by mail in order to ask if they are willing to participate in the control group of the study.(3) Subsequently all duly completed questionnaires at t0 will be checked for in- and exclusion criteria which are part of the initial self-administered questionnaire (Table 1).(4) Included study participants will then be recontacted to ask for follow-up data at t3, t6 and t12 (follow-up data will be gathered from all controls as the availability of economic data at t0 is temporally delayed for 12 month for organizational reasons).(5) The final statistical twins (1:1 matching) will be selected using Propensity Score Matching (PSM). According to Austin, the propensity score can be explained as “the probability of treatment assignment conditional on observed baseline characteristics”. Matched-pairs are generated with nearest neighbor matching. “The nearest neighbor matching selects for matching to a given treated subject that untreated subject, whose propensity score is closest to that of the treated subject” [19]. Input variables for PSM are derived from the baseline data of the self-administered questionnaires (SAQ) as well as economic data from the insurance data base (IDB). The detailed matching procedure is described in the statistical part of this manuscript.Feasibility of recruitmentThe selection of statistical twins is designed according to a successful procedure of a previous study of the insurance company. In this study on the efficacy of an exercise program for patients with back pain, a responder rate of the controls of 60 % could be achieved [18].

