#### Control group (CO)

CO receives general care. Participants of the control group may attend other offers of the health insurance company. Interventions are not restricted. However physical activity along the study period is monitored via self-administered questionnaires.

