#### Matching procedures and statistical analysis of clinical endpoints

The matching procedure for the statistical twins of the control group (CO) will be conducted as followed: ten statistical controls for each participant of the intervention group will be selected from the insurance data base according to the matching criteria displayed in Table 5. If it is not possible to select ten matches for a subject of the intervention group according to the criteria and tolerances displayed in Table 5, the tolerance will be extended in an iterative manner (steps of 100 Euro or 1 day respectively) until ten controls can be extracted from the data base.

**Table 5 Tab5:** Matching criteria to extract 10 controls for each participant of the intervention

Criteria	Tolerance
Co-morbidity: Quantity of hierarchical ordered morbidity groups in the previous year	0
Osteoarthritis of the hip or knee joint in the previous year: yes/no	0
Participation in a special general practitioner care program (“Hausarztzentrierte Versorgung”): yes/no	0
Routine data: Age (years), gender, type of insurance (compulsorily insured, family insured, pensioner, unemployed), complexity of work (from 1 = low to 4 = high), level of education (1 = no graduation to 4 = High School), highest level of educational attainment (from 1 = no qualification to 6 = doctoral degree), contractual form (permanent/fixed term contract, full time/part time)	0
Joint replacement in the last 24 month prior t0 at the hip and/or knee joint(s): yes/no	0
Sum of unspecific health care costs (overall costs) in the last 24 month prior t0: Sick-pay, hospital costs, out-patient costs, costs related to periods of disability and costs related to drugs, physical modalities and adjuvants.	+/− 100 EUR
Sum of unspecific health care costs (overall costs) in the last 6 month prior t0 (tm6): Sick-pay, hospital costs, out-patient costs, costs related to periods of disability and costs related to drugs, physical modalities and adjuvants.	+/− 100 EUR
Sum of specific diagnosis (hip/knee OA) related health care costs in the last 24 month prior t0: Sick-pay, hospital costs, out-patient costs, costs related to periods of disability and costs related to disease related drugs, physical modalities and adjuvants such as walkers, cranks or orthotics.	+/− 100 EUR

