Referring to the first point it has to be mentioned that all participants of the study are allowed to take part in additional health care offers. This holds true for participants of the control group as well. They may also attend the hip and knee training under study within the follow-up phase. This cannot be prohibited as all insurance holders have the same rights to participate in health care services offered. The exclusive participation in the assigned intervention (supervised exercise versus matched pair control group) can therefore only be guaranteed for the first 3 month of the study. This timeframe is also relevant for the evaluation of the primary outcomes. To control for potential confounders related to additional health care interventions, all follow-up questionnaires ask for participation in any course or training offer.

Although follow-up data for two years will be gathered in the context of this trial, statements on the effect of the intervention in the long run such as time to surgery and disease specific health care costs may be hampered. If 24-months evaluations are positive in terms of study outcomes, a protocol amendment for a 5-year follow up may be considered.

This study has 80 % power for unfavorably high cluster effects, in realty probably more than 90 % power to detect clinical relevant changes in the primary outcomes of the trial. Aside from clinical outcomes, cost-utility measures are of special interest in this study. Yet economic outcomes are expected to have much smaller effect sizes. We therefore decided to include all eligible patients, willing to participate in the trial, to increase power for the economic evaluation.

In due consideration of the burden of OA from an individual as well as economic perspective, the importance to evaluate the effectiveness and cost-efficiency of conservative treatment strategies is obvious. This applies in particular for lifestyle interventions such as physical exercises as they can be carried out by the patient himself and are therefore of special importance in the treatment of chronic diseases such as OA. Results of this trial will document accurately the effects of exercises on clinical and economic outcomes as well as safety aspects in a health care setting on the basis of a large sample size. As such, results of this trial should provide externally valid exercise recommendations in hip or knee osteoarthritis.

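### The Discussion guarantees exclusive participation up to t3, but no stated rule for the control group supports that guarantee

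*Protocol article*

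**What the plan says.** The limitations part of the Discussion says that exclusive participation "can therefore only be guaranteed for the first 3 month of the study" and ties that window to the primary outcomes. On control attendance at the study training it says: "They may also attend the hip and knee training under study within the follow-up phase". The reason given is: "This cannot be prohibited as all insurance holders have the same rights to participate in health care services offered".

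The section Control group (CO) says: "Participants of the control group may attend other offers of the health insurance company. Interventions are not restricted". It adds that physical activity is monitored by questionnaire. The request to refrain from other treatment between t0 and t3, under Interventions, is addressed to the intervention group alone.

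On who may train, the Design section makes membership of the insurer a prerequisite and adds: "Patients refraining from the study still are eligible to receive the exercise program". On who may be a control, the matching section says that "ten statistical controls for each participant of the intervention group will be selected from the insurance data base".

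**The concern.** A guarantee covering the primary-outcome window is a stated property of the design, and readers will rely on it when they interpret the t3 contrast. The rules printed in the same article do not produce it. Controls and non-study trainees come from the same insured population, and no listed criterion separates them.

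A control who takes the training between t0 and t3 receives part or all of the effect under test, so the difference in pain and function shrinks. A control who trained before t0 is not the intended comparator either, because any gain already sits in the baseline WOMAC scores that enter the propensity score. The results paper could also repeat an exclusivity claim that the design does not secure.

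**Working it through.** **1. The provisions side by side**

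| Provision | Who | What it does for t0 to t3 |
|---|---|---|
| Discussion, guarantee | both groups | asserts exclusivity |
| Discussion, equal-rights reason | all insurance holders | has no time limit, so applies before t3 as well |
| Control group (CO) | controls | no restriction, no time window |
| Interventions | intervention group only | a request to refrain |
| Table 1 | both | does not list the hip and knee training |
| Table 5 | control candidates | the only care programme listed is the general practitioner programme |
| Propensity score inputs | both | health-programme participation at t0 is balanced, not excluded |
| Follow-up questionnaires (Discussion) | both | record any course, exclude nobody |

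The last two rows are the stated safeguards. They balance or record exposure; neither prevents it.

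**2. How exposure could arise**

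- The Design section expects 1500 bookings and about 700 study participants: 1500 − 700 = 800 trainees outside the study (750 to 900 from the stated 50–60% pre-study loss).
- Places remain on the article's own figures: 85 courses × 12 places × 2 terms = 2040, less 1500 booked = 540.
- Control extraction runs quarterly, follows the entry of intervention participants, and spans two course terms with recruitment to March 2016 (Timelines). A control matched to a first-term participant could have a t0–t3 window that overlaps a second-term course. This is inferred; the article gives no dates for control t0.

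**3. The plan's own sample size, reproduced**

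Inputs from Sample size: effect size 0.3, two-sided alpha 0.025, power 0.90, dropout 20%, intra-class correlation 0.33, four study subjects per course.

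- n = 2(2.2414 + 1.2816)² / 0.3² = 276 per group; the exact t calculation gives 278, as stated.
- 278 / 0.80 = 348 (stated 350).
- Design effect 1 + 3 × 0.33 = 1.99; 350 × 1.99 = 697 (stated 700).

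**4. Illustration of dilution**

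Let c be the share of controls who receive the full effect; the article gives no value. The diluted effect is d = 0.3(1 − c), and power = Φ(d/SE − 2.2414). Evaluable subjects: 700 × 0.80 = 560 per arm.

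- Clustering in the intervention arm only: SE = √(1.99/560 + 1/560) = 0.0731.
- Factor 2 in both arms: SE = √(2/280) = 0.0845.

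| c (assumed) | d | Clustering in intervention arm only | Factor 2 in both arms |
|---|---|---|---|
| 0 | 0.300 | 96.9% | 90.5% |
| 5% | 0.285 | 95.1% | 87.1% |
| 10% | 0.270 | 92.7% | 83.0% |
| 20% | 0.240 | 85.2% | 72.5% |

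The article states the inflation factor for the intervention, which favours the third column.

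**5. Outer bounds for c**

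If all 800 non-study trainees were among the 10 × 700 = 7000 invited controls, c = 800/7000 = 11%. If all of them also responded while overall response was 60% (4200 people), c = 800/4200 = 19%. Both are extremes.

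**The case against.** Much of the opposing case stands.

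- **Intent.** The control group section speaks of other offers, and the Discussion places control attendance at the study training in the follow-up phase. The authors evidently intend no such use before t3. An intention is still not a rule, and the equal-rights reason works against it.
- **A condensed article.** A filter at data extraction may sit in the full protocol. One may therefore not conclude that nothing keeps trainees out, only that no mechanism is stated and that the stated sentences conflict.
- **The 800 are not 800 likely controls.** By the article's own account they are people who did not want to join the study or failed its criteria. Controls must also consent, and they are checked against Table 1. Table 5 requires exact agreement on age, gender, education and work. If the 800 were spread over 20,000 candidates (an assumption), c would be 4% and power with factor 2 in both arms about 88%; over 100,000 it would be 0.8% and about 90.0%.
- **Entry hurdles.** Joining a course needs a physician's prescription. That limits uptake but does not rule it out.
- **Recording.** The t3 questionnaire already asks about courses, so the data for a sensitivity analysis are planned.
- **Comparator and direction.** Controls receive general care and were never described as untreated. Dilution within the window cannot create a false benefit.

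A reader might also infer earlier exposure from the instructor training in 2014. The article documents no course before September 2015, so this is not supported.

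**Conclusion.** The point holds as an unsupported guarantee. For the primary-outcome window the article asserts an exclusivity that its rules do not provide, and no listed criterion removes users of the training from the control pool.

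Exposure between t0 and t3 biases the primary contrast towards no difference. Its size cannot be derived from the article and is probably small. The power losses shown are illustrations that assume the exposed share and a full effect in exposed controls. A reader might infer from them that power really falls to 83% or lower. The documents do not support that: no exposed share is given, and the lower figures need the inflation factor in both arms. Nor do the documents show that any control will in fact attend before t3.

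It is worth acting on because the remedy is cheap and the affected contrast is the primary one.

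**What to change.** 1. **Before matching.** At the 10:1 extraction, and again before the 1:1 matching, drop control candidates with a record of booking or attending the hip and knee training on or before their own t0. Apply this to controls only: intervention participants register before their t0 questionnaire, so the same filter would empty that arm. For the intervention group, exclude only people who completed an earlier course, if any ran. The filter uses information up to t0, so it respects the rule that no follow-up data are analysed before the twins are fixed.
2. **After t0.** Keep controls who start the training between t0 and t3 in the primary analysis, because removing them would select on events after baseline. Report their number from the t3 questionnaire or the insurer's records, and add one sensitivity analysis for this exposure.
3. **Wording.** Reconcile the control group section with the Discussion by replacing the guarantee with a statement of what the rules deliver.

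Cost: a slightly smaller control pool, buffered by the 10:1 extraction; a link between course bookings and the data base, which may take work because registration happens at the local sites; one extra analysis; and a change of wording.

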### Data privacy, ethics approval and consent to participate

Data privacy is warranted by including different parties to guarantee pseudonymization of patient data derived from different data sources. Each party has a predefined right of access to personal and study data of the participants. Only one independent party has access to personal insurance data as well as study outcomes. All other parties only have access to personal data or study data. Data privacy was approved by the data protection officer of the insurance company.

All participants of the exercise program receive a postal mailing prior to the first training session. This mailing includes information on the aims and the content of the study as well as on data privacy: in case of study participation, consolidation, analysis and utilization of data is carried out with random names only. The mailing further includes the informed consent form and the outcome questionnaire. The selected subjects from the insurance data base for the control group receive a similar mailing. Interested persons of the intervention as well as control group are informed that they confirm their informed consent by returning the informed consent form for data privacy and the pseudomyzed outcome questionnaires by post. Patients are informed about the voluntariness of study participation at all times. Participants of the exercise program are further informed that study participation is not a requirement for participation in this health care offer.

Ethical approval has been obtained from the Ethics Committee of the University of Tuebingen (Vote number 421/2015BO1).

Study data are erased after the legal retention period according to privacy policy apart from data that were already analyzed and recorded as study report and/or publication.

## Abbreviations

BMI: Body Mass Index
CBA: Cost-Benefit Analysis
CEA: Cost-Effectiveness Analysis
CEA: Incremental Cost-Effectiveness Ratio
CO: Control group
CUA: Cost-Utility Analysis
FITT: Frequency, Intensity, Time and Type (of exercise interventions)
GSE: General Self-Efficacy scale
HKT: Group-based hip and knee training in combination with a structured home-exercise program
ICUR: Incremental Cost Utility Ratio
IDB: Insurance data base
IG: Intervention group
MM: Exercises for motor learning/mobilization
OA: Osteoarthritis
PC: Exercises to improve postural control
PSM: Propensity score matching
QALY: Quality adjusted life years
S: Exercises for strength training
SAQ: Self-administerd questionnaire
VR-12: 8-scale questionnaire to measure health related quality of life
WOMAC: Western Ontario and McMaster Universities Osteoarthritis Index
